## Abstract

**Background:**

These trials are the first randomised controlled trials of telephone-based
weight management and healthy lifestyle interventions for low back pain and
knee osteoarthritis. This article describes the protocol and statistical
analysis plan.

**Method:**

These trials are parallel randomised controlled trials that investigate and
compare the effect of a telephone-based weight management and healthy
lifestyle intervention for improving pain intensity in overweight or obese
patients with low back pain or knee osteoarthritis. The analysis plan was
finalised prior to initiation of analyses. All data collected as part of the
trial were reviewed, without stratification by group, and classified by
baseline characteristics, process of care and trial outcomes. Trial outcomes
were classified as primary and secondary outcomes. Appropriate descriptive
statistics and statistical testing of between-group differences, where
relevant, have been planned and described.

**Conclusions:**

A protocol for standard analyses was developed for the results of two
randomised controlled trials. This protocol describes the data, and the
pre-determined statistical tests of relevant outcome measures. The plan
demonstrates transparent and verifiable use of the data collected. This
*a priori* protocol will be followed to ensure rigorous
standards of data analysis are strictly adhered to.

## BULLET POINTS

Lifestyle factors such as overweight and obesity are associated with low back
pain and osteoarthritis. However, accessible interventions aiming to support
patients with low back pain or osteoarthritis to manage lifestyle factors
have not been tested in high quality trials.The two trials determine the effectiveness of telephone-based healthy
lifestyle interventions for low back pain and osteoarthritis of the
knee.This protocol comprehensively describes key trial methodology relating to
data capture, management and pre-determined statistical analyses.Such protocols are important in raising the validity of physical therapy
research as they demonstrate transparent and verifiable use of the data
collected and ensure rigorous standards of data analysis are strictly
adhered to.

## Introduction

This protocol describes the first randomised controlled trials (RCT) of
telephone-based weight management and healthy lifestyle interventions for low back
pain and knee osteoarthritis. Here we describe the protocol and pre-determined
statistical analysis plan, for both trials (trial one: *low back
pain* and trial two: *knee osteoarthritis*). The protocol
and statistical analysis plan was finalised prior to analysing the data and will be
adhered to in analysing the data from the trials. All study investigators signed and
approved the statistical analysis plan in May 2016. Participant recruitment for both
trials was completed in October 2015, and final participant follow-up was completed
in May 2016. Following data integrity checks the database will be locked (June
2016). The statistical analyses specified in the statistical analysis plan will be
performed in June 2016.

## Study overview

### Study design and setting

These trials were established as part of a cohort multiple RCT design^1^, whereby participants from our existing cohort of patients referred for
an outpatient orthopaedic consultation at a public tertiary referral hospital
within NSW Australia, were randomised to be offered a new clinical intervention
(intervention group) or remain as part of the cohort (control group). Both
trials were prospectively registered with the Australian New Zealand Clinical
Trials Registry (trial one: ACTRN12615000478516, and trial two:
ACTRN12615000490572) and full study protocols for each trial have been published
elsewhere^2^
^,^
^3^. These trials were approved by the Hunter New England Health Human
Research Ethics Committee (13/12/11/5.18), Wallsend NSW, Australia and the
University of Newcastle Human Research Ethics Committee (H-2015-0043),
Newcastle, Australia.

### Participants and recruitment

Patients with non-specific low back pain (trial one, n=160) or knee
osteoarthritis (trial two, n=120) were recruited. Participants in the
intervention group of both trials were provided with brief advice and education
about the benefits of weight loss and physical activity for their conditions by
trained telephone interviewers. Additionally, participants in the intervention
group of trial one (low back pain) were provided with an initial consultation
with the study physical therapist. The consultation involved a low back pain
clinical assessment and detailed low back pain education based on clinical
practice guidelines. Behavioural change techniques were also utilised to support
a healthy lifestyle and weight management for low back pain. There was no
baseline clinical assessment for participants of trial two (knee
osteoarthritis).

Following baseline data collection, participants in the intervention groups of
both trials were referred to the NSW Get Healthy Information and Coaching
Service (GHS). The GHS is a free, telephone-based government funded service to
support individuals to modify their eating behaviours, increase their physical
activity, reduce alcohol consumption and achieve or maintain a healthy
weight^4^. The GHS has been shown to be effective in the general population and
involves 10 individually tailored coaching calls delivered over a 6-month period
by a university-qualified health professional. The support provided is based on
national guidelines and utilises motivational interviewing^4^. All health coaches were provided with training by a study investigator
(CW) in evidence-based management for low back pain and knee osteoarthritis.

Participants in the control group received any usual care offered to them by
their treating clinician during the six month intervention period, and
participated in data collection. Follow-up lasted for 26 weeks (6 months).

### Inclusion/exclusion criteria

Patients were eligible for inclusion in the trials if all of the following
criteria were met:

•Trial one condition definition: chronic low back pain defined as pain in
the lower back (i.e. between the 12th rib and buttock crease)
with/without leg pain and duration of longer than 3 months since the
onset of pain^5^;•Trial two condition definition: complaint of pain in the knee due to knee
osteoarthritis (as per referral) lasting longer than 3 months;•Aged 18 years or older;•Classified as overweight or obese with a self-reported body mass index
(BMI) ≥27kg/m^2^ and <40kg/m^2^;•Have access to and can use a telephone; and•Have back or knee pain, for each trial respectively, severe enough to
cause at least average pain intensity ≥3 of 10 on a 0–10 numerical
rating scale (NRS)^6^ in the last week or moderate level of interference in activities
of daily living (adaptation of item 8 on SF36)^7^.

Patients were excluded if they met the following criteria:

•Known or suspected serious pathology as the underlying cause of back pain
or knee osteoarthritis, for each trial respectively, (e.g. fracture,
cancer, infection, inflammatory arthritis, infection, cauda equine
syndrome);•A previous history of obesity surgery;•Current participation in any prescribed, medically supervised or
commercial weight loss program;•Back or knee surgery, for each trial respectively, in the last 6 months
or booked in for surgery in the next 6 months;•Unable to walk unaided;•Unable to comply with the study protocol that requires them to, adapt
meals or exercise, due to non-independent living arrangements;•Any medical or physical impairment, apart from back pain or knee
osteoarthritis for each trial respectively, precluding safe
participation in exercise such as uncontrolled hypertension, or morbid
obesity (BMI≥40); and•Unable to speak and read English sufficiently to complete the study
procedures.

### Unblinding

The analysis plan was written and approved prior to analysis of data and blind to
group status. Dummy coded variables representing group allocation will be used
to ensure blinding of statistician(s) undertaking the analysis.

## Objectives

The primary objective of both trials is to establish if:

Trial one: pain education and referral to a telephone-based weight management and
healthy lifestyle intervention improves pain intensity in patients with *low
back pain*, who are overweight or obese, compared to usual care.

Trial two: referral to a telephone-based weight management and healthy lifestyle
intervention improves pain intensity in patients with *knee
osteoarthritis*, who are overweight or obese compared to usual care.

Secondary aims of the two trials is to establish if the telephone interventions lead
to reductions in disability, weight, BMI, waist circumference, alcohol consumption,
and smoking prevalence, and improvement in quality of life, emotional distress,
sleep quality, physical activity, diet, pain attitudes and beliefs, perceived change
in condition and change in health care and medication use.

A separate analysis plan will be detailed for health economic analyses and is not
included in this manuscript.

### Definition of outcome variables

#### Participant demographics and baseline characteristics

Baseline data includes: age, gender, Aboriginal and/or Torres Strait Islander
status, employment status, country of origin, highest level of education,
health insurance status, other co-existing medical conditions needing
medication, and pain duration (how long have you been troubled with your
pain). Length of time waiting for consultation (days) and triage
classification will be obtained from hospital records. In Australia,
patients referred for orthopaedic consultation are categorised according to
urgency of consultation: urgent – to be seen within 30 days; semi-urgent –
to be seen within 90 days; and non-urgent – to be seen within 12 months^8^. See Table 1 for
details.

**Table 1 t01:** Demographic and baseline characteristics.

	**Intervention**	**Control**
**Demographic**		
Age (years)	mean (SD)	mean (SD)
Gender (male)	n/N (%)	n/N (%)
Aboriginal and/or Torres Strait Islander status	n/N (%)	n/N (%)
Employment status		
Employed	n/N (%)	n/N (%)
Unemployed	n/N (%)	n/N (%)
Retired	n/N (%)	n/N (%)
Can’t work (health reasons)	n/N (%)	n/N (%)
Country of origin (Australia)	n/N (%)	n/N (%)
Highest level of education		
>High school	n/N (%)	n/N (%)
Private health insurance	n/N (%)	n/N (%)
Other co-existing medical conditions needing medication	n/N (%)	n/N (%)
Length of time waiting for consultation (days)	mean (SD)	mean (SD)
Triage classification		
Non-urgent	n/N (%)	n/N (%)
Semi-urgent	n/N (%)	n/N (%)
**Baseline characteristics**		
Pain intensity (NRS)	mean (SD)	mean (SD)
Pain duration (how long have you been troubled with your pain)	mean (SD)	mean (SD)
Disability and function (Trial 1: RMDQ / Trial 2: WOMAC)	mean (SD)	mean (SD)
Subjective weight	mean (SD)	mean (SD)
BMI	mean (SD)	mean (SD)
Quality of Life (SF12.v2)		
Physical component score (PCS)	mean (SD)	mean (SD)
Mental component score (MCS)	mean (SD)	mean (SD)
Emotional distress (DASS-21)	mean (SD)	mean (SD)
Poor sleep quality (item 6, Pittsburgh Sleep Quality Index)	n/N (%)	n/N (%)
Physical activity (mins MVPA/week)	mean (SD)	mean (SD)
Diet		
Fruit (serves)	n/N (%)	n/N (%)
Vegetables (serves)	n/N (%)	n/N (%)
Discretionary foods (serves)	n/N (%)	n/N (%)
Alcohol consumption (AUDIT)	mean (SD)	mean (SD)
Smoking prevalence	n/N (%)	n/N (%)
Pain attitudes (SOPA)	mean (SD)	mean (SD)
Fear avoidance beliefs (FABQ)	mean (SD)	mean (SD)
Health care utilisation		
Medication use for back or knee pain	n/N (%)	n/N (%)
Visits for back or knee pain	n/N (%)	n/N (%)

NRS=numerical rating scale; RMDQ=Roland Morris Disability
Questionnaire; WOMAC=Western Ontario and McMaster Universities
Index; BMI=Body Mass Index; SF12.v2= Short Form Health Survey
version 2; PCS=Physical Component Score; MCS=Mental Component
Score; 21=Depression Anxiety Stress Scale;
MVPA=Moderate-to-Vigorous Physical Activity; AUDIT=Alcohol Use
Disorders Identification Test; SOPA=Survey of Pain Attitudes;
FABQ=Fear Avoidance Beliefs Questionnaire.

#### Primary outcome

The primary outcomes are average weekly back pain intensity (trial one) and
average weekly knee pain intensity (trial two), measured over the course of
follow up.

Participants were asked to report the “average pain intensity experienced in
their back (trial one) or knee (trial two) over the past week, on a 0 to 10
NRS, where 0 was ‘no pain’ and 10 was the ‘worst possible pain’”^6^. These pain intensity scores were measured at baseline, at 2, 6, 10,
14, 18, 22 and 26 weeks. Average weekly (back or knee) pain intensity is
defined as the Area under the Curve (AUC) of the pain intensity trajectory,
over the follow up period. The AUC for each participant will be computed
using the trapezoid rule.

#### Secondary outcomes

The secondary outcomes include:

•Physical disability and function, measured in trial one using the
Roland Morris Disability Questionnaire (RMDQ)^9^ 0-24 scale and measured in trial two using the Western
Ontario and McMaster Universities Osteoarthritis Index (WOMAC) 0-96
scale^10^;•Self-reported weight (kg);•Objective weight (kg) measured to the nearest 0.1kg by a trained
research assistant using International Society for the Advancement
of Kinanthropometry (ISAK) procedures^11^;•BMI calculated as weight /height squared (kg/m^2^)^12^;•Waist circumference measured by a trained research assistant using
ISAK procedures taken at the level of the narrowest point between
the inferior rib border and the iliac crest using a flexible tape
measure to the nearest 0.1 cm^11^;•Quality of life, measured using the physical and mental health
component scores from the 12-item Short Form Health Survey version 2
(SF12.v2)^7^;•Global perceived change in symptoms, measured using the Global
Perceived Effect (GPE) scale (-5 ‘vastly worse’ to 5 ‘completely
recovered’)^13^;•Emotional distress, measured using the Depression Anxiety Stress
Scale-21 (DASS-21) 0-63 scale^14^;•Sleep quality, measured using item 6 from the Pittsburgh Sleep
Quality Index (response options: very bad, fairly bad, fairly good,
very good)^15^;•Physical activity, measured using the Active Australia Survey^16^, reported as the average minutes spent participating in
moderate-to-vigorous physical activity (MVPA) per week;•Diet, measured using a short food frequency questionnaire (FFQ)^17^, reported as serves of fruit (0-1, 2 or more), serves of
vegetables (0-2, 3-4, 5 or more), serves of discretionary foods
including processed meats, salty snacks, takeaway meals, sweet or
savoury snacks, confectionary and sugar sweetened beverages (more
than once per week, once per week or less);•Alcohol consumption measured using the Alcohol Use Disorders
Identification Test (AUDIT) 0-12 scale^18^;•Smoking prevalence (have you smoked any tobacco in the last 4 weeks?
(this can include cigarettes, roll your own, pipes, cigars or any
other tobacco products))^19^;•Attitudes and beliefs, measured using the Survey of Pain Attitudes
(SOPA)^20^; and the physical component of the Fear Avoidance Beliefs
Questionnaire (FABQ) 0-24 scale^21^; and•Health care utilisation for each trial respectively, including back
or knee pain medication use (name), type of health service utilised
for back or knee pain including number of sessions, and attended
orthopaedic consultation or received surgery.

See Table 2 for data collection time
points for secondary outcomes.

**Table 2 t02:** Secondary outcome measures.

**Construct**	**Measurement**	**Time-point (weeks)**
Disability and function	Trial one: Roland Morris Disability Questionnaire (RMDQ)^9^ Trial two: Western Ontario and McMaster Universities Osteoarthritis Index (WOMAC)^10^	0, 6, 26 0, 6, 26
Subjective weight	Self-reported weight (kg)	0, 6, 26
Objective weight	Measured to the nearest 0.1kg^11^	0^a^, 26
BMI	BMI calculated as weight/height squared (kg/m^2^)^12^	0, 6, 26
Waist circumference	Measured to the nearest 0.1cm^11^	26
Quality of life	Short Form Health Survey version 2 (SF12.v2)^7^	0, 6, 26
Perceived change in condition	Global Perceived Effect scale (–5 to 5 scale)^13^	6, 26
Emotional distress	Depression Anxiety Stress Scale-21 (DASS-21)^14^	0, 26
Sleep quality	Item 6 from the Pittsburgh Sleep Quality Index^15^	0, 6, 26
Physical activity	The Active Australia Survey^16^	0, 6, 26
Diet	Short food frequency questionnaire^17^	0, 6, 26
Alcohol consumption	Alcohol Use Disorders Identification Test (AUDIT)^18^	0, 6, 26
Smoking prevalence	Self-reported current smoking status^19^	0, 6, 26
Pain Attitudes	Survey of Pain Attitudes (SOPA)^20^	0, 6, 26
Fear avoidance beliefs	Fear Avoidance Beliefs Questionnaire (FABQ)^21^	0, 26
Health care utilisation	Medication use for back (trial one) or knee pain (trial two) Visits for back (trial one) or knee pain (trial two) – type and number of sessions Attended orthopaedic consultation, received surgery	0, 6, 26 0, 6, 26 26

a Intervention group of low back pain patients (trial one) only.
BMI: Body Mass Index.

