#### Treatment allocation

Eligible patients were randomised in a 1:1 allocation ratio, to either
receive the weight management and healthy lifestyle intervention at that
time (intervention group) or remain as part of the cohort and be told they
will be offered clinical services in 6 months (control group). The
randomisation schedule was generated a priori by an independent statistician
using SAS 9.3 through the SURVEYSELECT procedure. To randomise patients, a
trained interviewer opened a sealed opaque envelope containing group
allocation. A staff member not involved in the study prepared the
envelopes.

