### Secondary analysis

Between group differences in the trajectory of pain intensities over the
follow-up period will be examined using growth curve modelling. Hierarchical
linear models will be used, with fixed effects for treatment group, time, and
the interaction between the two. The model will include random subject-level
intercepts and slopes. A linear growth trend will initially be assumed, and if
not appropriate different functional forms for the trend will be applied (for
example the square root transformation). If an appropriate functional form
cannot be determined a flexible piecewise linear model will be used^26^. We will also investigate treatment effect heterogeneity that may exist
in latent subgroups of participants through growth mixture models^27^. In these models a number of latent classes are specified that model the
potential for participants to have different trajectory types, the functional
forms identified from the previous growth curve analyses will inform the
functional forms for this analysis. The model will include the following random
effects that are all conditional trajectory class membership: intercept linear
slope and quadratic slope. The random effects are influenced by the treatment
group, so there will potentially be 3 lots of treatment effects (for each random
effect) for each latent class.

Longitudinal generalised linear mixed models will be used to assess treatment
effect on post randomisation secondary outcome measurements with random
intercepts for individuals to account for correlation of repeated measures and
an appropriate link function dependent on the type and distribution of the data.
We will compare the adjusted mean change (continuous variables) or relative
risks (dichotomous variables) in outcome from baseline to each time point
between the treatment and control groups. A binomial distribution family (with
log link) will be used for dichotomous outcomes (sleep quality, smoking
prevalence), and a Poisson or negative-binomial distribution family (with a log
link function) will be used for count outcomes (health care utilisation) based
on assessment of data dispersion. T-tests will be used to test between group
differences in variables collected only at 26 weeks (objective weight, BMI,
waist circumference). See Table 4 for
details.

**Table 4 t04:** Secondary outcomes.

**Outcome**	**Intervention**	**Control**	**Intervention - control**
Disability and function (Trial 1: RMDQ / Trial 2: WOMAC)			

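### The plan does not fix which weight builds BMI, so the self-reported weight and BMI rows are open to arm-dependent reporting error or to mixed measurement methods

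*Protocol article*

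**What the plan says.** The Secondary outcomes section of the protocol article lists three related variables: "Self-reported weight (kg"; "Objective weight (kg) measured to the nearest 0.1kg by a trained" research assistant; and BMI, defined in the list as "BMI calculated as weight /height squared (kg/m^2" and again in Table 2 as "BMI calculated as weight/height squared (kg/m^2^)^12". Neither definition names the weight.

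Table 2 schedules self-reported weight and BMI at weeks 0, 6 and 26, and objective weight at weeks 0 and 26. A footnote limits the week-0 objective measurement: "Intervention group of low back pain patients (trial one) only". Table 4 repeats this layout and adds an Overall row for self-reported weight and for BMI.

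The Secondary analysis section assigns t-tests to "differences in variables collected only at 26 weeks (objective weight, BMI" and waist circumference. BMI at screening is self-reported: "Classified as overweight or obese with a self-reported body mass index". The Sample size section calls weight the key secondary outcome without saying which weight variable is meant. Under Analysis principles, secondary outcomes are significant at p≤0.01.

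**The concern.** Reductions in weight and BMI are stated aims, and weight is the key secondary outcome, so it should be clear which results rest on a scale and which on a participant's report.

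The arms differ in ways that could affect reporting. The intervention arm is offered 10 coaching calls over 6 months that deal with eating, activity and weight, and those receiving the calls know it. Controls receive usual care and are told they "will be offered clinical services in 6 months (control group"). If the arms misreport weight by different amounts after randomisation, the difference appears as a treatment effect or conceals one. Because BMI from reported weight is the same report divided by height squared, one artefact could give two results that seem to confirm each other.

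**Working it through.** **Where measured weight exists (Table 2 and its footnote)**

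| | Week 0 | Week 6 | Week 26 |
|---|---|---|---|
| Trial one, intervention | reported and measured | reported | reported and measured |
| Trial one, control | reported | reported | reported and measured |
| Trial two, both arms | reported | reported | reported and measured |

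BMI can therefore rest only on self-report at week 6 in every arm, and at baseline in trial one's control arm and both arms of trial two. The source is open at week 26 in all arms and at week 0 in trial one's intervention arm.

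**What each reading implies**

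1. *Week-26 BMI self-reported.* A reporting difference of b kg between arms shifts the BMI contrast by b/height². For 1 kg this is 1/1.8² = 0.31 to 1/1.6² = 0.39 kg/m²; for 2 kg it is 0.62 to 0.78.
2. *Week-26 BMI measured.* The week-26 contrast is free of reporting error. Within-arm change is not: under-reporting of 1-2 kg at baseline adds 0.35-0.69 kg/m² to the change in both arms at a height of 1.70 m. The Overall row then combines a week-6 contrast exposed to reporting error with a week-26 contrast that is not.
3. *Trial one's measured baseline weight used for BMI in the intervention arm.* The method then differs by arm at baseline. If both arms under-report by u kg, the difference in change moves by u in favour of the intervention. With self-reported week-26 weight, the intervention change is too low by u; with measured week-26 weight, the control change is too high by u.

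**The plan's own weight figure**

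The Sample size section states 80% power for a 6% weight reduction but gives no SD, so the figure cannot be reproduced. Solving backwards, with 0.85×80 = 68 and 0.85×60 = 51 evaluable per arm and two-sided alpha 0.025:

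- detectable difference in SD units = (z₀.₉₈₇₅ + z₀.₈₀)×√(2/n) = 0.53 (trial one) and 0.61 (trial two);
- implied SD = 6%/0.529 = 11.3% and 6%/0.611 = 9.8% of mean weight. At an assumed mean of 90 kg this is about 10.2 and 8.8 kg.

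**False-positive rate with no true effect**

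Assumptions not in the documents: a reporting difference b of 1 or 2 kg, and an SD of the analysed value from 4 kg (plausible for a change score) to 15 kg (plausible for raw weight). SE = SD×√(2/n). The rate at the 0.01 level is 1 − Φ(2.576 − b/SE) + Φ(−2.576 − b/SE).

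| | b | SD 4 | SD 6 | SD 10 | SD 15 |
|---|---|---|---|---|---|
| Trial one, n = 68 | 1 kg | 13.2% | 5.5% | 2.4% | 1.6% |
| | 2 kg | 63.3% | 26.4% | 7.9% | 3.6% |
| Trial two, n = 51 | 1 kg | 9.5% | 4.2% | 2.0% | 1.4% |
| | 2 kg | 48.0% | 18.6% | 5.9% | 2.9% |

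Example: n = 68, SD 4, b = 2 gives SE = 4×√(2/68) = 0.686, b/SE = 2.915 and a rate of 63.3%. A t cut-off lowers the rates slightly (62% for this cell). An error in the opposite direction hides a true effect of the same size.

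**The case against.** Much of the protection is already in the plan. Measured week-26 weight is a secondary outcome in both arms with its own t-test and Table 4 row, measured waist is compared as well, and self-reported weight is labelled as subjective in the tables. A spurious self-reported loss would sit beside an objective comparison. This stands, and it limits the point to the self-reported weight and BMI rows.

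The article also refers to full protocols published elsewhere, where the derivation of BMI could be given. That would excuse silence, but not the conflict here between the Secondary analysis section and Tables 2 and 4.

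A reader might infer more than the documents support:

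- *That week-26 BMI is self-reported.* The shared schedule with self-reported weight points that way; the grouping with objective weight and waist points the other way.
- *That every reading biases the comparison between arms.* With measured week-26 weight, the week-26 contrast is not biased by baseline misreporting, because baseline assessment preceded randomisation and its error is equal between arms in expectation.
- *That trial one's intervention participants anchored later reports on a scale reading.* Nothing says they were told the reading, or that it followed their self-report. The order is only inferred from a one-arm measurement alongside a baseline assessment done before randomisation.
- *That false-positive rates of tens of per cent are to be expected.* They need a 2 kg difference and an SD of 4-6 kg. At SD 10, close to what the power statement implies, the rates are 2.0-7.9%.

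**Conclusion.** The point holds in limited form. The source of weight in BMI is unstated, the article points both ways, and each way of filling the gap leaves some weight or BMI rows hard to interpret. The planned week-26 comparison of objective weight is unaffected, so the documents do not support a claim that the trials' weight results as a whole are unreliable.

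The size and direction of any reporting error are unknown. Under the stated assumptions the false-positive rate for a self-reported row ranges from about 1.4%, close to the nominal 1%, to 63%. The value of acting lies less in that range than in the fact that data already collected can remove the ambiguity and show whether the arms report differently.

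**What to change.** 1. Reconcile the Secondary analysis section with Tables 2 and 4 by defining two variables: self-reported BMI (weeks 0, 6 and 26) and measured BMI (week 26). Do not mix them in one change score or Overall row. Do not use trial one's one-arm measured baseline weight in any between-arm comparison.
2. Base the week-26 conclusions on weight and BMI on measured weight in both arms. Replace the unadjusted t-test with linear regression on arm, adjusted for self-reported baseline weight or BMI. That covariate precedes randomisation, so its error does not bias the contrast, and adjustment reduces residual variance by a factor of about 1 − r², where r is its correlation with the week-26 value. Label the self-reported contrasts as supportive.
3. Report self-reported minus measured weight at week 26 by arm, with the between-arm difference and 95% CI, as a descriptive check beside the self-reported results.

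The cost is plan wording and one extra table row, with no new measurements. The downside is that week-6 and Overall results for weight and BMI become supportive only, and measured BMI is missing for anyone not measured at week 26.
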